#### Neuropsychological evaluation

Participants will be evaluated on the following neuropsychological tests by trained doctors:Mini-Mental State Examination (MMSE), Chinese version translated by Mingyuan Zhang: evaluates time and place orientation, attention and calculation, recall, language, and copying. Scores range from 0 to 30 points, with a lower score indicating worse cognitive function.Montreal Cognitive Assessment (MoCA), Beijing version: evaluates visual-spatial ability, executive function, naming, memory, attention, language, abstraction, and orientation. Scores range from 0 to 30 points, with a lower score indicating worse cognitive function.The Stroop Color word test (CWT), Huashan version: evaluates semantic activation, dominant response inhibition, attention, working memory, and information processing speed. The time spent in each card and the number of errors will be recorded. A longer time cost or more errors indicate worse cognitive function.The digit span test (DST), a subtest of the Chinese version of the Wechsler Adult Intelligence Scale-Revised: evaluates immediate memory and attention. A shorter string of repeated numbers indicates worse cognitive function.

### Grouping and follow-up plan design

During the baseline period, all participants will be evaluated by intelligent gait analyzer and neuropsychological tests. According to the intelligent gait report, each patient will be classified as normal gait group or abnormal gait group. All participants will be naturally observed for at least 1 year, and all their medical behaviors will be recorded. At six months after enrollment, all patients will be interviewed by telephone to collect falls events, cerebrovascular events, and the changes in medical behaviors during the follow-up period. The participants will be invited to undergo intelligent gait assessment and neuropsychological evaluation in the hospital at 12 months after enrollment, and falls events, cerebrovascular events, the changes in medical behaviors during the follow-up period will be collected. The details are presented in Fig. 1 and Table 1. All data will be encrypted and stored on the local server in Zhongshan hospital.

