**Fig. 1 Fig1:**
[figure not shown]
Flow diagram of the ACCURATE-2 study

**Table 1 Tab1:** Overview of the study assessments

Assessment	Baseline	Six months	One year
Method	Face to face	Telephone	Face to face
Cranial MRI	×		×
Intelligent gait assessment	×		×
Neuropsychological evaluation			
MMSE	×		×
MoCA	×		×
CWT	×		×
DST	×		×
Falls events	×	×	×
Cerebrovascular events		×	×
Changes in treatment		×	×

× indicates that the assessment took place. *CWT* the Stroop Color Word Test, *DST* the Digit Span Test, *MMSE* Mini-Mental State Examination, *MoCA* Montreal Cognitive Assessment

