### Outcomes

The primary outcome of this study will be the changes in the MMSE score in patients with SCD after 1-year follow-up.

The secondary outcomes of this study will be the changes in intelligent gait parameters (step length, gait speed, step frequency, step width, standing up time, and turning back time) and the changes in scores on other neuropsychological tests (MoCA, CWT, and DST) after 1-year follow-up, the prevalence of abnormal gait and cognition decline in patients with SCD, and the incidence of cerebrovascular events and falls in patients with SCD.

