### Statistical analysis

All measurement data will be tested using the Shapiro-Wilk normality test. Normally distributed continuous measurement data will be expressed as mean and standard deviation, while non-normally distributed measurement data will be expressed as median and interquartile range. The t-test, Wilcoxon signed-ranks test, repeated measures t-test, or linear generalized model will be used to compare measurement data. The enumeration data will be expressed as a composition ratio or rate. The chi-square test or Fisher exact method will be used to compare enumeration data. Pearson linear correlation analysis or Spearman correlation analysis will be performed for correlation analysis. Survival will be estimated using a Kaplan-Meier survival curve. The propensity score matching method will be used to minimize the influence of other confounders. Subgroup analyses will include region and hospital levels. All cases with missing values will be deleted. A significant difference will be identified *P* < 0.05.

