SCD is a type of cerebrovascular disease diagnosed according to its neuroimaging features and clinical manifestations [17, 18]. However, it is not cost-effective and feasible to screen asymptomatic elderly people and follow up patients with SCD using routine cranial MRI. Even with symptomatic strokes, approximately 90% of patients in China underwent non-contrast brain CT, while only 50% underwent brain MRI [24]. Therefore, it is very important to develop a specific quantitative screening and evaluation method for the clinical characteristics of patients with SCD. Gait assessments is expected to become a promising evaluation method for patients with SCD: it not only evaluates the degree of gait disorders, but also predicts the risk of long-term cognitive decline and other adverse outcomes. Verghese et al. [25] found that the hazard ratio of vascular dementia for non-dementia individuals with neurological gait abnormalities at baseline was 3.46 (95% CI, 1.86–6.42) after a median 6.6-year follow-up. Dumurgier et al. [26] proposed that a patient’s gait was slow up 7 years prior to dementia, and those with a greater decline in gait speed had a higher risk of developing dementia. Similarly, Montero-Odasso et al. [27] reported that greater changes in dual-task gait speed in patients with mild cognitive impairment were associated with dementia progression. The population-based RUN DMC Study [28] reported that for every 0.1 m/s decrease in gait speed, the hazard ratio of 8-year mortality in patients with SCD was 1.15 (95% CI, 1.06–1.24). Most of the above-mentioned studies use sensors to measure gait parameters, with the disadvantage that the equipment is expensive and difficult to apply in primary hospitals. Future investigations should focus on early screening methods for high-risk population to effectively reduce the burden of dementia, falls, and stroke in SCD. Our intelligent gait analyzer can quantify gait parameters and classify gait pattern with high-precision based on intelligent pose estimation algorithm, which is expected to be further applied in primary hospitals, communities and even families. Moreover, most previous large-scale population-based SCD studies were conducted in developed countries, and the patients were mostly White. Our study includes Chinese multi-ethnic yellow race, which may provide more clues for the early detection and prevention of SCD.

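### Events in months 6 to 12 have one stated route, an invited hospital visit, and death is not collected, so the incidence of cerebrovascular events and falls is liable to be underestimated

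*Protocol article*

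**What the plan says.** The Protocol article sets the contact mode visit by visit.

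- **Month 6** (Grouping and follow-up plan design): "At six months after enrollment, all patients will be interviewed by telephone to collect falls events, cerebrovascular events" and changes in medical care.
- **Month 12** (same section): "The participants will be invited to undergo intelligent gait assessment and neuropsychological evaluation in the hospital at 12 months after enrollment". The sentence goes on: "falls events, cerebrovascular events, the changes in medical behaviors during the follow-up period will be collected".
- **Table 1**: the row for contact mode reads "Method Face to face Telephone Face to face", for baseline, six months and one year. "Cerebrovascular events" are marked at six months and one year. There is no row for death or vital status.
- **Outcomes**: one secondary outcome is "the incidence of cerebrovascular events and falls in patients with SCD". Death is not listed.
- **Statistical analysis**: "Survival will be estimated using a Kaplan-Meier survival curve", with no event named. The same section removes any case that has missing values.
- **Sample size**: a 20% loss is allowed for in a total of 1600.

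**The concern.** The month-12 visit requires the patient to travel to hospital, walk the TUG course and complete four neuropsychological tests. Someone with a disabling stroke or a serious fall injury in the preceding six months is poorly placed to do this, and someone who has died cannot. Whether an event is recorded then depends partly on how severe it was. Month 6 does not share this weakness to the same degree, because a telephone call does not depend on mobility.

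Two features add to the problem. Without vital status and dates of death, a fatal cerebrovascular event has no defined way into the count, and a death from another cause cannot be told apart from ordinary loss to follow-up. If the deletion rule is applied across analyses, a stroke properly reported by telephone at month 6 is also lost when the patient has no month-12 test scores.

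At stake are the incidence figures and any time-to-event analysis. The Discussion offers the study as a source on the epidemiology of adverse outcomes in this disease. An event that was never sought cannot be recovered later by analysis.

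**Working it through.** **1. The plan's own figure.** The only figure that can be recomputed is the sample size, and it rests on MMSE change alone. Inputs from Sample size: declines of 0.5 (SD 0.5) and 0.7 (SD 1.2), ratio 2:1, power 90%, alpha 0.05 (taken as two-sided), 20% loss.

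- Abnormal gait: (1.960 + 1.282)² × (1.2² + 0.5²/2) / 0.2² = 411.1, so 412. Normal gait: 2 × 412 = 824.
- After loss: 412/0.8 = 515 and 824/0.8 = 1030, in total 1545. Rounding each group up to the next 50 gives the stated 550 and 1050.

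Event rates do not enter, so this point leaves sample size and power unchanged.

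**2. How many people could be affected.** 1600 × 0.20 = 320. This is an upper figure. It treats the whole planning allowance, set for the MMSE comparison, as non-attendance at month 12.

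**3. Share of events missed.** The article gives no event rate, timing or severity. Assumptions:

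- true 12-month cerebrovascular incidence p, illustrated at 2% (1600 × 0.02 = 32 events);
- half of events in months 6 to 12;
- a share f of events, 20% to 60%, fatal or disabling enough to prevent attendance, half of these fatal;
- all other patients with events attend.

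| Scenario | Share missed | Range for f = 20% to 60% | True 2.0% of 1600 is seen as |
|---|---|---|---|
| (a) Only severe month 6–12 events missed | f/2 | 10% to 30% | 1.8% to 1.4% |
| (b) As (a), plus fatal month 0–6 events that no proxy reports | f/2 + f/4 | 15% to 45% | 1.7% to 1.1% |
| (c) All severe events lost because these patients are deleted | f | 20% to 60% | 1.6% to 0.8% |

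The shares missed do not depend on p. At p = 1% (16 events) or 4% (64 events) they are the same.

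**4. Denominator.** The last column keeps all 1600 in the denominator. If deletion in (c) also reduces it to 1600 − 320 = 1280, the seen rate is 25.6/1280 = 2.0% at f = 20% and 12.8/1280 = 1.0% at f = 60%. With an attenders-only denominator, bias therefore arises only when patients with events attend less often than the cohort as a whole.

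**5. Cross-check by another route.** Suppose non-attenders have three times the attenders' month 6–12 risk and the true month 6–12 risk is 2%. Then attenders' risk is 2% / (0.8 + 0.2 × 3) = 1.43%, which is 29% low for that half-year. If an equal 2% falls in months 0–6 and is fully captured, the year shows 3.43% against 4%, about 14% low. That lies within the range in (a).

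**6. Contrast between gait groups.** Take assumed 12-month risks of 3% (abnormal) and 1.5% (normal), a true ratio of 2.0, with half of events in months 6–12.

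- Late loss 40% and 20%: 3% × 0.8 = 2.4% and 1.5% × 0.9 = 1.35%, ratio 1.78.
- Equal loss: ratio 2.0.
- Late loss 20% and 40%: 3% × 0.9 = 2.7% and 1.5% × 0.8 = 1.2%, ratio 2.25.

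The direction follows entirely from the assumed difference in loss.

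**The case against.** The strongest reply is that this is silence rather than error. The article condenses a fuller protocol. Tracing, proxy contact and vital-status checks may be set out there or in Fig. 1, which is not shown. The text says that events will be collected without limiting this to attenders, and that participants are observed and their medical care recorded for at least a year. Face to face in Table 1 may simply be the mode needed for MRI, gait video and testing.

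Part of this stands. It cannot be said that non-attenders will not be contacted, only that no route to them is stated. But the article does not leave contact mode open. It assigns one mode to each visit, with the wider-reaching mode at month 6 and the narrower at month 12. Death is absent from both the outcome list and the assessment schedule.

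Three stronger readings are tempting, and the document does not support them.

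- **That fatal and disabling strokes are bound to drop out.** Non-fatal strokes in months 0 to 6 can be reached by the telephone interview, and relatives may report some fatal ones. The loss is a risk.
- **That a mortality curve is planned with no deaths to plot.** Survival may mean time free of a fall or cerebrovascular event. The firm defect is that the event and the handling of death are undefined.
- **That the gait-group contrast is biased toward no difference.** The Discussion cites another study in which "the hazard ratio of 8-year mortality in patients with SCD was 1.15" per 0.1 m/s slower gait. That is background over eight years. It shows nothing about one-year attendance by group here, where entrants must walk unaided. The groups come from a normal/abnormal classifier, not from speed alone, and the incidence outcome is stated for the whole cohort.

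**Conclusion.** The point holds as a risk of under-ascertainment in a secondary outcome. As written, the plan has one stated route to falls and cerebrovascular events in months 6 to 12, and that route is least open to the people with the worst events. Death is not collected, and the deletion rule can remove events already reported. The incidence outcome is therefore liable to be too low.

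The size cannot be derived from the document. Under the stated assumptions on timing and severity, about 10% to 30% of 12-month events would be missed, rising to 20% to 60% if month-6 reports are deleted along with incomplete cases. These are illustrative ranges, not estimates. Any effect on a comparison of gait groups depends on whether such loss differs between them, which the document does not show. The primary MMSE outcome, as far as this point goes, and the sample size are untouched. The change is worth making because it is cheap and the information cannot be retrieved afterwards.

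**What to change.** 1. For anyone who does not attend at month 12, apply the month-6 telephone method: ask the patient, or a contact person named at baseline, about falls, cerebrovascular events and vital status, with dates.
2. Add death, with date and cause, to Table 1, and count fatal cerebrovascular events as events.
3. Keep month-6 event reports in the incidence analysis even when month-12 tests are missing, and limit the deletion rule accordingly.
4. Name the event for the Kaplan-Meier analysis. End time at risk at the last contact at which event status was obtained, and treat other deaths as a competing event.

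**Cost:** up to about 320 extra calls across 14 sites that already plan to call all 1600 patients at month 6, plus one contact field on the baseline form. Proxy reports will be less detailed than an interview in clinic, especially for minor falls, so the source of each report should be recorded. If a fuller protocol already contains a tracing procedure, stating it in the follow-up section and Table 1 would settle items 1 and 2.

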**Fig. 1 Fig1:**
[figure not shown]
Flow diagram of the ACCURATE-2 study

**Table 1 Tab1:** Overview of the study assessments

Assessment	Baseline	Six months	One year
Method	Face to face	Telephone	Face to face
Cranial MRI	×		×
Intelligent gait assessment	×		×
Neuropsychological evaluation			
MMSE	×		×
MoCA	×		×
CWT	×		×
DST	×		×
Falls events	×	×	×
Cerebrovascular events		×	×
Changes in treatment		×	×

× indicates that the assessment took place. *CWT* the Stroop Color Word Test, *DST* the Digit Span Test, *MMSE* Mini-Mental State Examination, *MoCA* Montreal Cognitive Assessment

### Outcomes

The primary outcome of this study will be the changes in the MMSE score in patients with SCD after 1-year follow-up.

The secondary outcomes of this study will be the changes in intelligent gait parameters (step length, gait speed, step frequency, step width, standing up time, and turning back time) and the changes in scores on other neuropsychological tests (MoCA, CWT, and DST) after 1-year follow-up, the prevalence of abnormal gait and cognition decline in patients with SCD, and the incidence of cerebrovascular events and falls in patients with SCD.

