#### Inclusion criteria

Aged 60–85 years.Diagnosed with SCD according to the 2016 statement issued by the American Heart Association and the American Stroke Association [17]:

(A)Absence of clinically recognized acute stroke symptoms.(B)Cranial MRI taken in the past 1 year having shown one of the following (according to STRIVE [18]):Lacunes of presumed vascular origin: defined as a subcortical, round, or ovoid fluid-filled cavity with a diameter of 3–15 mm showing a low central signal and irregular marginal high signal on T2 fluid-attenuated inversion recovery (T2-FLAIR). The central signal is similar to that of cerebrospinal fluid, and the distribution is consistent with the blood supply area of the perforating artery. Fazekas scores should be ≥2 points.WMH of presumed vascular origin: defined as hyperintensity on T2-FLAIR in the white matter area (periventricular or subcortical), the signal of which differs from cerebrospinal fluid. Fazekas scores should be ≥2 points.Microbleed: defined as a small round area devoid of signal with associated blooming on susceptibility weighted imaging or T2-weighted imaging generally 2–10 mm in diameter. Microbleed lesion number should be ≥5.
(3)Conscious and able to finish all neuropsychological test.(4)Ability to stand and walk independently without waking aids, and complete the intelligent gait assessment.(5)Sign the informed consent form.

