#### Intelligent gait analysis (SAIL system)

The vision-based artificial intelligent gait analyzer we proposed (named SAIL system) includes a data acquisition client and a data analysis server. The data acquisition client consists of a laptop and an RGB-depth camera. The computer application we designed can record the entire TUG test by calling the RGB-depth camera, and upload the video files subsequently to the data analysis server via the network. The data analysis server will detect gait spatiotemporal parameters and walking pattern classification for each patient through the built-in intelligent algorithm and transmits the analysis report back to the data acquisition client through the network.

The TUG videos will be recorded in a bright, clean, and tidy indoor square area (at least 3.8 m × 3.8 m) without any obstruction. A armless chair with standard seat height will be placed on one side, and a visible colored line on the floor will mark a distance of 3 m from the seat. The RGB-depth camera on a 1.2-m-high tripod will be placed 3.8 m away in a vertical line from the midpoint of the footpath. The patients will be required to wear well-fitting trousers and a pair of everyday flat shoes, take off the long coat that reaches the hips, put down the items in their hands, and remove their backpacks before the TUG test. Each participant will be asked to sit on the chair first, stand upon hearing the doctor’s instructions, walk straight to the 3-m mark, turn around, return to the chair, and sit down finally. All participants will complete the TUG test twice at their usual comfortable walking pace, and at least a five-minute break will be given between the tests. Participants can practice 1–2 times to familiarize with the walking test requirements.

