### Sample size

Referring to previous studies of cognitive decline among patients with SCD [19–23], we assume that the MMSE score will decrease by 0.5 ± 0.5 points in the normal gait group and 0.7 ± 1.2 points in the abnormal gait group within 1 year; the ratio of abnormal gait to normal gait among outpatients with SCD is 1:2. Test efficiency 1-beta is set at 90%, while test level alpha is set at 0.05. An estimated 20% shedding rate, sample size of 1050 patients with a normal gait and 550 patients with an abnormal gait will be required. Therefore, a total of 1600 patients will be included.

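### Patients who can no longer perform the 12-month walking test for a health reason are deleted from the gait-change outcomes, so those outcomes describe only people still able to walk

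*Protocol article*

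**What the plan says.** - **Outcome.** The Outcomes section lists as secondary outcomes the "changes in intelligent gait parameters (step length, gait speed, step frequency, step width, standing up time, and turning back time") after one year. It gives no category for a patient who cannot be tested.
- **Entry.** The Inclusion criteria require "Ability to stand and walk independently without waking aids, and complete the intelligent gait assessment". Every participant therefore starts with a usable gait measurement.
- **Test.** Under Intelligent gait analysis (SAIL system), the patient must "put down the items in their hands, and remove their backpacks before the TUG test", then stand, "walk straight to the 3-m mark, turn around, return to the chair, and sit down finally". The six parameters and the normal/abnormal class are all derived from that video.
- **Timing.** There is one follow-up gait test: participants are "invited to undergo intelligent gait assessment and neuropsychological evaluation in the hospital at 12 months after enrollment". Contact at six months is by telephone (Table 1).
- **Missing data.** The Statistical analysis section has a single rule, with no exception: "All cases with missing values will be deleted".
- **Attrition.** The Sample size section allows for "An estimated 20% shedding rate" and does not break it down by reason.

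**The concern.** Because everyone can walk and complete the test at entry, inability for a health reason at 12 months is new deterioration. The study expects events that could cause it, since it counts falls and cerebrovascular events as outcomes. Such a patient may still attend and complete the cognitive tests. What is missing is a number from the video; the patient's gait state has been observed, and it is among the worst possible. The plan handles this like any other missing value and removes the patient from the outcome meant to measure gait decline.

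Two things are at stake. First, the reported gait changes apply only to patients still able to walk at one year. Second, the deletion rule refers to 'cases'. If that means whole patients, a missing gait test would also remove an observed 12-month MMSE change from the primary analysis.

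**Working it through.** **Step 1: follow one patient through the plan.** Take a patient who cannot walk at 12 months but attends and completes the MMSE.

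| Step | Section | Result |
|---|---|---|
| Baseline gait | Inclusion criteria | present |
| 12-month TUG | Grouping and follow-up plan design; SAIL system | no completed video |
| Six parameters and gait class | SAIL system | none can be derived |
| Change in gait | Outcomes | undefined; no 'unable' category |
| Analysis | Statistical analysis | deleted |

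The result is certain for a patient who cannot do the test. It is not certain for one who walks with an aid at 12 months. The no-aid condition is an entry criterion, and the test description does not mention aids at follow-up.

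**Step 2: size for the gait outcomes.** The protocol states no figure for these outcomes, so there is none to reproduce. Let q be the proportion unable at 12 months and m the number of SDs by which their deterioration exceeds that of patients still tested. Both are assumptions. For a patient who cannot walk, m is only a notional severity, used to show scale.

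Mean over all = mean in those tested + q × m (in SDs, in the direction of worsening), so the completers-only mean understates deterioration by q × m.

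| q | m = 1 | m = 2 | m = 3 |
|---|---|---|---|
| 1% | 0.01 | 0.02 | 0.03 |
| 3% | 0.03 | 0.06 | 0.09 |
| 5% | 0.05 | 0.10 | 0.15 |
| 10% | 0.10 | 0.20 | 0.30 |

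With the same m in both groups, the contrast shifts by (q_abnormal − q_normal) × m. At 5% and 1% this is 0.04 × m, or 0.04 to 0.12 SD. At 10% and 2% it is 0.08 × m, or 0.08 to 0.24 SD. At equal rates it is zero.

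**Step 3: reach to the primary outcome, only if 'cases' means whole patients.** The protocol plans 550 abnormal and 1050 normal. After 20% loss, 550 × 0.8 = 440 and 1050 × 0.8 = 840 remain. The assumed MMSE scores "decrease by 0.5 ± 0.5 points in the normal gait group and 0.7 ± 1.2 points in the abnormal gait group", a difference of 0.2. Power is taken as Φ(0.2/SE − 1.96), with SE = √(1.2²/n_abnormal + 0.5²/n_normal) and a two-sided 0.05 level assumed.

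- Plan as stated: SE = √(1.44/440 + 0.25/840) = 0.0598; power 91.7%, consistent with the stated 90%.
- 5% and 1% of attenders also deleted: 22 and about 8 patients, leaving 418 and 832; power 90.5%.
- 10% and 2% deleted: 44 and about 17 patients, leaving 396 and 823; power 89.0%.

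The loss of power is slight. What matters is that the deleted patients are selected by gait deterioration, and their MMSE results are already in hand.

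**The case against.** The strongest objection is that the gap is narrow and possibly negligible. The Exclusion criteria remove severe gait or balance disturbance and several disorders that affect walking, so loss of walking within a year may be rare in both groups. Falls and cerebrovascular events are collected without a TUG, so part of the deterioration is captured elsewhere. The choice between a worst-rank and a completers-only analysis is often left to the analysis plan, which is not shown. All of this bears on size and priority and is accepted there. It does not remove the defect, because the protocol states a rule, deletion without exception, and that rule gives the wrong treatment for these patients.

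Four stronger readings are tempting, and the documents do not support them.

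- *Every patient who comes to need an aid has no gait value.* Aid use at 12 months is not addressed.
- *These patients necessarily leave the gait–cognition analysis.* The groups are defined by baseline gait, which every participant has. The Study design section correlates gait parameters with changes in cognitive scores without saying at which visit gait is taken. With baseline gait, these patients drop out only under the whole-patient reading of 'cases'.
- *Inability is commoner in the abnormal group.* This is plausible but stated nowhere.
- *The bias can be put in metres per second by scoring inability as speed 0.* Such a figure rests entirely on chosen inputs. Assume baseline speeds of 0.7 (abnormal) and 0.9 (normal) m/s, a change of −0.03 m/s in those tested, and 0.5% unable in the normal group, whose mean is then 0.995 × (−0.03) + 0.005 × (−0.9) = −0.034. With 1% unable in the abnormal group its mean is −0.037 and the group difference about −0.002 m/s. With 5% it is −0.064 and the difference about −0.029 m/s. Zero is also a poor score for someone who may still walk with a stick.

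**Conclusion.** The point holds in a limited form. A patient unable to perform the 12-month test for a health reason is dropped from the six gait-change outcomes. Those outcomes then describe only patients still able to walk and understate deterioration, provided that those who became unable worsened more than those tested. The group contrast is biased as well if inability differs between groups.

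The size cannot be determined from the documents. The 0.01 to 0.30 SD range rests wholly on assumed rates and severities, and over one year the true value may lie at the low end. The effect on the primary outcome is conditional on reading 'cases' as whole patients. Deletion within each analysis is an equally possible reading, so this calls for clarification and is not an established error in the primary analysis. No change to the sample size follows.

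**What to change.** 1. In Statistical analysis, state that deletion applies per analysis, so that a missing 12-month gait test never removes observed MMSE, MoCA, Stroop or digit span scores.
2. At 12 months, record why a gait test is missing (health inability, technical failure, refusal or death) and report the numbers by group. State also whether a patient who now uses an aid is to be tested.
3. Count health inability as abnormal gait in any 12-month prevalence of abnormal gait.
4. For the six gait-change outcomes, add a rank-based group comparison that gives health inability the worst rank, reported alongside the completers-only change in original units. Do not assign these patients a gait speed of 0.

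The cost is one reason code at the visit and a few sentences of analysis text. The reason should be recorded at the visit because it may not be recoverable later. The drawback is that the rank-based result is less direct to express in metres or seconds, which is why the completers-only change stays beside it.
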